#### Qualitative data and analysis

Data from parent diaries, focus groups and interviews will be transcribed and thematically analysed. A partially inductive and partially deductive (based on themes from our pilot study [30]) coding frame will be developed, using the analytical stages of Braun and Clarke [63]. Qualitative analysis will be evaluated using indicators of confidence and relevance [64] to ensure rigour, transparency, and accountability.

#### Video coding

Research assistants or others qualified for research scoring of the instruments in question will code the 12-min video recordings of parent and child play with the DCMA and the BOSCC coding frameworks. They will regularly co-rate the videos to maintain inter-rater reliability. To account for natural inter-rater differences, the same rater will code the pre and post scores, blind to the time point.

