### Allocation and blinding

Individuals will be randomly allocated to the intervention or control group. Participants will be block-randomised, stratified by gender, by the web-based randomisation service Sealed Envelope™ [33], overseen by a trial statistician uninvolved in data collection. Upon obtaining written consent, a research assistant will access Sealed Envelope™ to obtain the treatment allocation, and will therefore be aware of each participant’s allocation, but will be blind to the time point of psychometric assessments at the data analysis stage. Due to the nature of the intervention participants cannot assuredly be blinded to treatment, as they will be aware of the app they are using. The rest of the research team, including the principal investigator and clinical lead, will be blinded to the allocation of each family.

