**Brief Observation of Social Communication Change (BOSCC)**

The BOSCC [47] is scored from a 12-min video recording of a parent-child play session, coded on 16 items assessing atypicality, frequency, and severity of autistic symptoms. The BOSCC coding scheme was developed from the Autism Diagnostic Observation Schedule (ADOS)-2 [48] by the same research team, to detect clinically significant changes in autistic symptoms following treatment. The BOSCC has yielded excellent inter-rater reliability and high test-retest reliability [47]. Treatment efficacy will be measured by differences in mean scores from baseline to post-intervention between the intervention and control groups.

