**Dyadic Communication Measure for Autism (DCMA)**

The DCMA [8] is coded from the same parent-child play session as the BOSCC, to assess dyadic communicative interaction between parent and child, making it largely complementary to the behaviours scored by the BOSCC. Independent codes are applied to instances of the parent’s synchronous responses with the child, the child’s initiations with the parent, and the time spent in shared attention. The mean change from baseline to post-intervention will be compared between the intervention and control groups.

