### Procedure

Participant eligibility will be assessed by the clinical lead, and staff under her direction. Research assistants will ascertain consent, allocate participants according to an independent randomisation procedure (https://SealedEnvelope.com/), and administer assessments, including recording a 12-min video of child and parent in free play for later scoring with the DCMA and BOSCC. The Principal Investigator (PI) received formal training in DMCA and BOSCC coding, which he passed on to the research assistants. The research assistants are trained to a high standard in psychometric and qualitative administration and coding, and receive regular supervision from the PI, the clinical lead, and qualitative specialist. Members of the research team responsible for data collection have completed CPFT Good Clinical Practice training. Parents will receive training to deliver the intervention and will be asked to keep a diary. Parents will be asked to complete the optional think-aloud session and focus group.

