#### Auditing

Trial conduct will be audited monthly by the PI and the clinical lead. In accordance with Good Clinical Practice, a site folder will be held at the City Care Centre within the CPFT Integrated Children’s Service, containing copies of correspondence with families, the protocol, and a delegation log specifying the responsibilities of research team members. Case report forms for each participant will be used to record personal information, treatment allocation, dates of assessments and iPad drop-off, and relevant information collected during telephone calls during the intervention period e.g*.* if the child was feeling sick. Recruitment data are uploaded monthly to the NIHR Clinical Research Network Portfolio by a research assistant so that CPFT can provide additional support if the trial falls behind schedule.

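### BOSCC and DCMA videos may be coded by research assistants who know the arm and filmed the visits; the only mask stated is to time point, and nothing protects it

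*Protocol article*

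**What the plan says.** The primary outcomes include five psychometric instruments: MSEL, BOSCC, DCMA, BPVS-III and SRS-2. Two of them come from one recording. "The BOSCC [47] is scored from a 12-min video recording of a parent-child play session", and the DCMA "is coded from the same parent-child play session as the BOSCC". For both, the change from baseline to post-intervention is compared between arms.

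The article says the following about who handles allocation, filming and coding:

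- **Allocation and blinding:** a research assistant obtains the allocation from the web service and so knows it, "but will be blind to the time point of psychometric assessments at the data analysis stage".
- **Procedure:** research assistants (plural) take consent, allocate, and "administer assessments, including recording a 12-min video of child and parent in free play".
- **Video coding:** "Research assistants or others qualified for research scoring of the instruments in question will code the 12-min video recordings". To deal with differences between raters, "the same rater will code the pre and post scores, blind to the time point".

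On the leads, Allocation and blinding states: "The rest of the research team, including the principal investigator and clinical lead, will be blinded to the allocation of each family". The Auditing section gives the same two leads a monthly audit of conduct. In the same paragraph it says: "Case report forms for each participant will be used to record personal information, treatment allocation, dates of assessments".

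**The concern.** The article describes masking in two places, and for the people who may code the videos both descriptions stop at time point. Staff who know the arm are among the permitted coders, and the same staff record the videos. Eight weeks of change in a child may not show a stranger which video came first. Someone who was in the room for both sessions may simply remember.

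A coder who knows both the arm and the order can, without intending to, score the later video of an intervention child more favourably. Because one rater scores both videos of a family, the shift goes straight into that family's change score. These two measures are scored from recordings and so are among the easiest in the trial to have rated by someone who does not know the arm.

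A second, smaller matter is that the leads' blinding is asserted, while the form that carries allocation is described in the section on their monthly audit. No step is given that keeps the two apart.

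**Working it through.** **The plan's own figure.** The only sizing figure is ±14% around a 62.8% recruitment rate with 46 families. It reproduces: 1.96 × √(0.628 × 0.372 / 46) = 0.140. It has no bearing on this point, and the article gives no SD, effect size or rater-error figure for BOSCC or DCMA.

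**Step 1: who can code, and what they know.**

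| Role | Assigned to | Knows arm? | Present at filming? |
|---|---|---|---|
| Obtains allocation | Research assistant(s) | Yes, stated | – |
| Films play session | Research assistants | Yes, if they also allocated | Yes |
| Codes video | Research assistants or other qualified scorers | Not excluded | Not excluded |

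No sentence prevents one person from filling all three rows for the same family. Equally, no sentence says that one person will.

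**Step 2: what time-point masking protects.** Let a coder who knows the arm add a shift s to the scores of an intervention family. If the coder cannot tell the videos apart, s falls on both, and the change is (post + s) − (pre + s) = post − pre. The shift cancels. The planned mixed-model analysis of variance has two time points, so its time-by-treatment term is this same comparison of change.

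**Step 3: what happens if the mask leaks.** Suppose the shift b is added only to intervention-arm post scores, and only when the coder recognises the later video, in a fraction f of families. The bias in the between-arm change is f × b.

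**Step 4: size, under assumed values.** The inputs are 23 per arm (from the article) and, as assumptions, no true effect and a change-score SD of 1. The standard error of the between-arm difference, in units of the change-score SD, is √(2/23) = 0.295. With a normal approximation, the two-sided false-positive rate is 1 − Φ(1.96 − fb/0.295) + Φ(−1.96 − fb/0.295).

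| Rater shift b (assumed) | f = 0 (mask holds) | f = 0.5 | f = 1 (always recognised) |
|---|---|---|---|
| 0.2 SD | 5% | 6% | 10% |
| 0.3 SD | 5% | 8% | 17% |
| 0.5 SD | 5% | 14% | 40% |

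For example, with b = 0.3 and f = 1, 0.3/0.295 = 1.02 standard errors, giving 17%. Neither b nor f can be taken from the article. The table shows the range and predicts nothing.

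**Step 5: the leads.** Allocation and blinding says they are blinded to each family's arm. Auditing says they audit monthly and that the case report forms hold allocation. It does not say that they open those forms, and it does not say that allocation is kept from them.

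**The case against.** The strongest reply has four parts.

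**The text does not say that unblinded staff code the videos.** Other qualified scorers are allowed, and Allocation and blinding speaks of a single research assistant who learns the allocation. A reader might infer that the coders will be the people who allocated and filmed each family. That is possible under the text but not stated. What stands is that nothing rules it out, and that Procedure gives allocation and filming to the research assistants as a group.

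**Time-point masking is a sensible mask for a change score.** A reader might say that only masking to arm matters in a comparison of arms. Step 2 shows otherwise: with one rater per family and the order truly hidden, a constant arm-related shift drops out. This part of the reply stands in full. The objection is only that the mask may not hold for someone who filmed the visits.

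**The audit conflict is an inference.** A reader might conclude that the leads see allocation every month, so that their blinding is contradicted. The Auditing section does not say this. What remains is a claim of blinding with no safeguard described.

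**This is a feasibility trial.** The Discussion says that it is too small to establish effectiveness. The scores feed forward largely through variance and missing data, and a constant shift leaves the variance within each arm unchanged. This limits the consequence considerably. It does not remove it: the outcome sections still compare arms, the BOSCC section calls that comparison a measure of efficacy, and the Aims include judging which measures are sensitive to change, which a rater shift could flatter.

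**Conclusion.** The point holds in a limited form. As written, the plan permits arm-aware staff who filmed the sessions to code two of the five primary psychometric instruments, and it relies on a time-point mask that may not hold for those staff. The resulting bias in BOSCC and DCMA change lies between zero (order truly hidden) and the full rater shift (order always recognised). Taking the upper end as the expected bias would go beyond the text. The size rests wholly on assumed values of the shift and of how often order is recognised.

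The lack of a safeguard for the leads' blinding is a gap to close and has not been shown to be a breach. The protocol should be changed on both matters, but neither undermines the recruitment, retention or fidelity aims. Confidence is medium, because actual coder assignments could be sound without the article saying so.

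**What to change.** **Video coding.** State that each family's two videos are coded in random order, after the post-intervention visit, by a trained coder who does not know that family's arm and did not allocate, support or film it. Waiting for the second visit is what makes random order possible. The plan already offers three sources of coders: the other qualified scorers it allows, the principal investigator (trained in both instruments according to Procedure), or a research assistant with no involvement with that family and no sight of its allocation. The same-rater rule and the time-point mask can stay.

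**Auditing.** Keep allocation in a restricted log, separate from the forms seen at audit, or withdraw the statement that the leads are blinded. If the principal investigator is to code, the first option is needed, since otherwise that coder's masking to arm is not secured.

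**Cost.** Some scheduling effort, and coding that starts later than it could. No extra visits, measures or participants are needed. Whether the research assistants can swap families depends on how many there are, which the article does not give; if they cannot, the other two sources remain.

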## Discussion

Point OutWords was developed in collaboration with children with autism and their therapists and caregivers [30], to include engaging jigsaws, high-contrast graphics, and exogenous cues to help capture and maintain attention, and customisable reinforcement prompts. The interface was adapted to accommodate open-loop visuomotor control (a visuomotor impairment common in people with autism), eliminating a major source of users’ frustration. Working from autistic cognitive strengths, Point OutWords aims to enhance motor skills and to promote representation of objects as sequences (of iconic puzzle pieces, symbolic letters, or symbolic sounds), prerequisite abilities that can support communicative development.

There is a need for therapies that address underserved subpopulations of autism and can be delivered with ease at a low cost. For children with autism who have motor impairment and greater receptive than expressive communication, our new intervention could fill this gap in services were it shown effective in a full-scale RCT. Before such a large-scale study can be framed, a feasibility trial is a necessary step to evaluate recruitment and retention rates and identify actions for reducing attrition. Feasibility trials are especially helpful if the proposed population, in this case, autism with motor impairment, has not previously been specifically tested [65]. Attrition poses a particular challenge with respect to the control group, but we hope that explaining the study’s contribution to science, regularly telephoning families to offer support, and offering the prospect of using Point OutWords after participation in the trial will motivate families to complete the study. As the acceptability of the control apps is a likely predictive factor in reducing attrition in the control group, with advice from parents of autistic children we have selected iPad apps that are enjoyable and fun for children and families. These control apps were selected based on the absence of Point OutWords skills and tasks, as the inadvertent involvement in similar therapy or training in a control group can confound results as recently reported in one large-scale trial [12].

Variance in outcome measures will be an outcome measure itself, used to inform on the suitability of certain psychometric assessments and the sample size in a full-scale RCT. The proportion of missing data in assessments will demonstrate which measures are acceptable to children and their caregivers. For example, in a previous study [19] children were not compliant with an oral motor assessment (Com DEALL Oro Motor Assessment [66]) possibly because of sensory sensitivities around the mouth. The last decade and a half of research on early intervention in autism has spurred the development of new measures sensitive to change from which the current trial benefits, such as the BOSCC [47] and the AIM [62]. Furthermore, we use a wide range of assessments to comprehensively ascertain the impact of the Point OutWords intervention, including measures of restricted and repetitive behaviour (BOSCC, SRS, AIM); some studies have found that improvement in communication skills can have a knock-on effect on the reduction of restricted/repetitive behaviours [9, 67]. Along the same lines, measuring an intervention’s outcomes, not just on autistic symptom severity but on individual and family well-being and daily functioning, has recently been underscored [68], so we include measures of parent stress (PSI), family quality of life (FQoL), and children’s challenging behaviour (maladaptive behaviour subdomain on VABS-2).

Qualitative data from diaries, interviews, and focus groups will help identify barriers to successful delivery of the intervention, allowing such issues to be resolved. The Point OutWords intervention is flexible therapy, not constrained to an environment or a time of day, which can be delivered when the child’s mood is most conducive to learning. Feedback about how Point OutWords slots into the daily family routine will be used to enhance the social validity of the intervention design.

As autism is a heterogeneous condition it is unlikely that one style of intervention will address all individuals, nor all aspects of its symptomatology within each individual. Our intervention for motor and communication skills facilitated by Point OutWords can complement other therapies that address communication and social skills more directly. Indeed, the answer will lie in cumulative effectiveness research and the use of common outcome measures across trials so that systematic reviews and meta-analyses can be easily conducted in the future [2]. The current trial prepares for this prospect, adopting measures such as the DCMA and BOSCC used in the PACT-G trial [69], and VABS-2 and the MSEL used in the Early Start Denver Model trial [12] and many other studies of autism. While the current trial is not sufficiently scoped to ascertain whether the Point OutWords intervention is effective in improving communication skills in children with autism, it can inform the design of larger RCTs, not only for Point OutWords but also for other early interventions in autism.

### Trial status

NIHR protocol number: 40703; Recruitment began on 12 March 2019 and is expected to be completed by December 2019.

### Monitoring

#### Trial Management Group and Patient Steering Committee

[name] (academic PI and overall project lead), [name] (clinical PI), [name] (parent co-investigator) and [name] (qualitative research specialist) will oversee the trial’s progress. The Trial Management Group will communicate amendments to testing or recruitment criteria to the rest of the research team. There are no interim analyses planned. In addition, we are setting up a Patient Steering Group comprising four parent representatives, which will convene quarterly. [name] heads the Patient Steering Group and will report to the Trial Management Group.

#### Adverse Effects

Research staff will monitor participants for adverse effects, such as stress associated with the intervention, during fortnightly telephone calls with participants. One possible adverse effect might arise from overuse of the iPad, to a degree that could displace reciprocal social interaction between child and parent. To address this possibility, parents will be reminded that Point OutWords is a joint activity involving them and their child, not just the technology and their child. Safety reporting for adverse effects will be followed in line with CPFT Good Clinical Practice.

#### Auditing

Trial conduct will be audited monthly by the PI and the clinical lead. In accordance with Good Clinical Practice, a site folder will be held at the City Care Centre within the CPFT Integrated Children’s Service, containing copies of correspondence with families, the protocol, and a delegation log specifying the responsibilities of research team members. Case report forms for each participant will be used to record personal information, treatment allocation, dates of assessments and iPad drop-off, and relevant information collected during telephone calls during the intervention period e.g*.* if the child was feeling sick. Recruitment data are uploaded monthly to the NIHR Clinical Research Network Portfolio by a research assistant so that CPFT can provide additional support if the trial falls behind schedule.

#### Dissemination

We aim to publish methodological lessons and quantitative and qualitative trial results in peer-reviewed scientific journals. Preliminary results would be presented at the 2020 annual meeting of the International Society for Autism Research. Our web site [16] will be updated to inform parents and clinicians of the trial findings. Findings will be reported at CPFT multidisciplinary meetings and at a meeting for individuals with autism, their families, teachers, and therapists. Findings will be added to our trial registration at ISRCTN. Per standard NIHR contractual terms, the trial’s funder will have authority over publication, such authority not to be unreasonably applied. CPFT as the Sponsor will not have authority over publication. Authorship is available to members of the project team, and on request to others who have referred patients (e.g. clinicians) or collected or analysed data (e.g. students). Each empirical publication will include a statement of author contributions. There will be no use of professional writers.

## Data Availability

Data sharing is not applicable to this article as no datasets were generated or analysed for this protocol study. Participant-level data will be available at a later date. Although no specific reuse of participants’ data in future studies is contemplated a priori*,* this possibility is allowed by the consent document except of course in instances where the parent has withdrawn their child’s data from the study: “By agreeing to participate in this study, you are giving us permission to release anonymous, non-identifying data to other researchers for their use in legitimate scientific research. These data may be posted on the World Wide Web for other scientists to download. At any time whilst the study remains ongoing – even after your child’s participation in the study may have ended – you may withdraw your consent, and in this case we would delete your data from the study dataset and from the set of anonymised data that we release in future.” No biological specimens will be collected for any outcomes.

## Abbreviations

ABA: Applied behaviour analysis
ADOS-G: Autism Diagnostic Observation Schedule - Generic
AIM: Autism Impact Measure
BOSCC: Brief Observation of Social Communication Change
BPVS-3: British Picture Vocabulary Scale III
Com DEALL: Communication developmental eclectic approach to language learning
CONSORT: Consolidated standards of reporting trials
CPFT: Cambridgeshire and Peterborough Foundation Trust
FQoL: Family Quality of Life Survey
MSEL: Mullen Scales of Early Learning
NHS: UK National Health Service
NICE: National Institute for Health and Care Excellence
NIHR: National Institute of Health Research
PSI-4: Parenting Stress Index IV
RCT: Randomised controlled trial
SRS-2: Social Responsiveness Scale II
VABS-2: Vineland Adaptive Behaviour Scales II
VMPAC: Verbal Motor Production Assessment for Children
